### Recruitment procedure

To ensure the inclusion of 1,152 patients, recruitment will take place at five study sites across Germany (Greifswald, Kiel, Leipzig, and Munich/Halle; Fig. 3). We estimate that (i) 30% of the GP patients between 60 and 77 years are eligible for the study (according to the FINGER trial, approximately 40% have the required CAIDE Dementia Risk Score ≥ 9 [30]; among these another 25% are estimated to be excluded according to the *AgeWell.de* exclusion criteria.). Based on previous experiences from other multi-centric trials [62, 63] and regarding the demanding nature of this prevention trial, we assume a rather conservative response rate of approximately 33%. Thus, every study site will screen *n* = 2,880 GP patients to identify *n* = 864 potentially eligible GP patients (except for Munich/Halle: half numbers due to shared recruitment between the two study sites). To ensure these numbers, we suggest a number of *n* = 24 GP practices per study site (*n* = 96 GP practices in total) as sufficient, leading to a total number of *n* = 12 patients that have to be recruited per GP practice. GP practices will receive monetary incentives for recruitment and provision of patients’ data.

**Fig. 3 Fig3:**
[figure not shown]
AgeWell.de recruitment of participants per study site

### Randomization

To ensure a balance in sample size across groups over time, block-randomization of the GP practices will be used with a targeted assignment ratio of participants to intervention A vs. B of 1:1. Participating GP practices (clusters) will be randomized either to intervention A or B. Randomization will be conducted at the data management center at the Institute for General Practice at the Hannover Medical School, using a randomization list that is concealed to the recruiting study sites.

### Blinding

Whereas blinding of interviewers and study nurses cannot be realized in *AgeWell.de*, GPs will be blinded towards their respective group allocation. Eligible participants will receive all necessary information about the study in an information sheet provided by the GP, including information on the components of both interventions and on the random assignment of participants to either intervention A or B. After signing an informed consent at the GP’s practice, participants will receive a letter from the study sites with information on their respective group allocation and on next steps of the study.

### Data collection

Each study center will be recruiting GP practices using an invitation letter with information on study design and aims as well as GPs’ duties during the trial. GPs interested in study participation can reply per fax or telephone. The recruiting study sites will then schedule a personal appointment at the GP practice to explain the recruitment procedure and to provide all necessary documents (informed consent form, patient information, screening sheets etc.).

Case finding and recruitment will be conducted by the GP practices. Data of regular GP patients will be screened by trained practice personnel in association with the *AgeWell.de*-study personnel, according to the inclusion and exclusion criteria. The GP will then provide all necessary information about the study to eligible patients. Patients who are interested in study participation will sign an informed consent. Contact information of the patients will be sent to the local recruiting centers. Next, patients who have consented to participate will receive a letter from the study personnel, informing them about their respective group allocation. Home visits for baseline assessment will be scheduled.

At baseline and at follow-up assessment after 24 months, fully structured interviews will be conducted with all participants, assessing the primary and secondary endpoints. Other relevant information assessed include sociodemographic information, subjective cognitive decline, self-reported impairments and symptoms, anthropometry, blood pressure, nutrition, physical activity, bereavement/grief, medication, vascular risks). Moreover, GPs will provide data on participants’ health characteristics (diagnoses, lab values, medication) using standardized questionnaires. To conduct the process evaluation, the success rate of recruitment (number of eligible GP patients, number of participants and non-participants, (baseline) characteristics of participants and non-participants, reasons for non-participation) will be provided by the GP practice personnel. Standardized telephone interviews on reasons for dropout will be held with intervention A-participants, if applicable. For participants in intervention A, additional interim sessions will be scheduled: one face-to-face assessment after 12 months at the participants’ home and five telephone calls after 2, 4, 8, 16, and 20 months, respectively (see Table 3). These fully structured interviews serve the purpose of monitoring adherence to the intervention and motivation (monitoring & booster sessions). Participants in intervention group A will be asked to track their activities in the intervention components using weekly diaries. To reduce non-response as well as dropout in *AgeWell.de*, interviewers will undergo training regarding all procedures and assessments, including motivational interviewing techniques [64]. Likewise, motivational tasks will also be carried out by the principal investigators (Table 1).

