Enhancement of social engagement	- Assessment of level of social activity and risk of social isolation - Information on the importance of an active lifestyle including high social engagement for dementia risk - Enhancement of social engagement will be planned together with each study participant individually
Bereavement, grief and depressive symptoms	- Assessment of depressive symptoms and underlying risk factors (e.g. bereavement, grief) - If necessary, participants will be encouraged to contact their GP and will be provided with adequate support and care (e.g. referring participants to groups, psychiatrists, psychotherapists, psychiatric hospitals). Additionally, participants will receive written information on addresses and helplines which can be contacted in case of grief and/or depressive symptoms. - If applicable, encouragement to use MoodGym – a scientifically developed and evaluated free web-based training program to prevent and reduce depressive symptoms (http://www.moodgym-deutschland.de/).
Motivational tasks across all components	- Personnel continuity regarding the contact person for the participants - Study nurses will be trained in motivational interviewing techniques and participants will be strongly encouraged to contact their contact person, whenever necessary - Birthday/Christmas/holiday cards originally signed by trial authorities/principal investigators - Participants of intervention A will receive a brochure including recommendations (additional tips and suggestions each week for an active lifestyle, e.g. recipes, suggestions for physical activity, and information on healthy ageing) as well as a weekly diary to track their activities in the intervention components.

Participants of intervention group B (basic) will receive *GP treatment as usual* (GPTAU) and *general health advice* (GHA) related to the components of intervention A. We hypothesize that the multi-component intervention program of intervention A will be superior to GPTAU and GHA (intervention B) regarding trial outcomes.

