### Outcomes

#### Primary endpoint

In accordance with previous trials [2, 5, 7], we will assess change in cognitive performance as the primary endpoint. Cognitive performance will be assessed with a neuropsychological test battery covering the six cognitive domains for diagnosing mild and/or major neurocognitive disorder according to DSM-5 (attention, executive function, learning/memory, language, perceptual-motor abilities, and social cognition). Composite cognitive *z-*scores based on the results from all single tests will be calculated. Single *z-*scores will be calculated using baseline mean and standard deviations and then, for the composite score, the single *z-*scores will be averaged.

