### Statistical analyses

Preliminary analyses involve three parts. First, data will be cleaned and checked for inconsistencies by statisticians at the central data management center to ensure data accuracy and coherence. Second, outcome variables will be examined to identify potential outliers and leverage points. Third, missing data will be inspected and handled according to patterns of data missingness, e.g., by multiple imputation [65].

A dropout analysis will be performed to test whether complete and incomplete cases differ according to relevant sociodemographic variables, potentially introducing selection bias.

Descriptive analyses will be carried out to examine differences in baseline measurements regarding the composite cognitive *z-*score (primary endpoint) and secondary endpoints between the two intervention groups. Additionally, single scores for the six neurocognitive domains will be calculated and analyzed. Suitable balancing techniques, such as entropy balancing, will be used for baseline measurements to warrant a high degree of comparability between study groups [66]. In order to analyze changes in primary and secondary endpoints of the two groups over time (treatment effect), latent growth curve modeling (LGM) will be utilized. Group membership (A vs. B) as well as other time-invariant characteristics will be assessed as predictors of change in cognitive performance in the models. Model estimates will be weighted using, for example, calculated entropy balancing weights to equalize possible baseline differences in covariates and outcomes. The models will further be stratified by age and gender to evaluate whether treatment effects on primary and secondary outcomes differ by subgroups.

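### Participants learn their allocation before the baseline cognitive tests, so the only pre-treatment value of the primary endpoint is open to arm-related effort and to arm-related loss

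*Protocol article*

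**What the plan says.** Two sections of the protocol article give the same order of events.

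- **Data collection:** the patient consents at the practice and contact details go to the local centre. The patient then gets a letter "informing them about their respective group allocation. Home visits for baseline assessment will be scheduled".
- **Blinding:** after consent, "participants will receive a letter from the study sites with information on their respective group allocation and on next steps of the study". The section opens with "Whereas blinding of interviewers and study nurses cannot be realized in" the trial. Of those in contact with participants, only the GPs are described as blinded.

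On the endpoint and its use:

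- **Primary endpoint:** "we will assess change in cognitive performance as the primary endpoint".
- **Data collection:** "At baseline and at follow-up assessment after 24 months, fully structured interviews will be conducted with all participants, assessing the primary and secondary endpoints". The 12-month visit and the interim calls are for arm A only and serve adherence and motivation.
- **Statistical analyses:** estimates may be weighted with "calculated entropy balancing weights to equalize possible baseline differences in covariates and outcomes", and missing data are handled according to their pattern, with multiple imputation as an example.
- **Randomization and Recruitment procedure:** whole practices are randomised from a list concealed from the recruiting sites, with 12 patients planned per practice.

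**The concern.** A baseline value is useful in a randomised comparison because allocation cannot have influenced it. Here it can, by two routes.

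1. **Effort and conduct of the tests.** Participants have been told the components of both programmes before consenting, so those allocated to B know what they will not receive. Trail Making, word-list memory and verbal fluency depend on effort. If effort at the baseline visit differs by arm because of the letter, the difference enters the change score.
2. **Loss between letter and baseline.** The Limitations section itself describes participation as demanding and expects this to raise dropout. Someone put off by arm A, or disappointed by arm B, can withdraw before the home visit. That person is consented and allocated but has no cognitive score, so those who reach baseline may differ by arm. The planned safeguards fit this poorly: telephone interviews on reasons for dropout are held with arm A only, and the attrition part of the process evaluation is framed around the follow-up period.

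Consent is obtained before the letter, so the letter does not affect who consents. Sending it before baseline gives part of that protection away.

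**Working it through.** **Order of events.** Both sections read: consent, allocation letter, baseline home visit. No passage places testing before the letter or provides a baseline assessor unaware of the arm. The design figure and the assessment schedule are not shown, so the order rests on the text.

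**Target and precision, from Sample size.** Control decline 0.21 z, SD 0.5, a 50% difference to be detected, two-sided 5%, 90% power, inflation factor 1.1, dropout 10%.

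- Target difference: 0.5 × 0.21 = 0.105 z.
- Reproducing the plan: n = 2 × (1.960 + 1.282)² × 0.5² / 0.105² = 477 per group (478 with the t distribution); the article states 475.
- 475 × 1.1 × 1.1 = 575, and 475 × 1.1 / 0.9 = 581; the article states 576. The planned size is reproduced closely enough.
- Effective number: 576 × 0.9 / 1.1 = 471 per group. SE of the difference in change = 0.5 × √(2/471) = 0.0326 z.

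The inflation factor of 1.1 is taken as stated.

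**Illustrative bias.** The documents give no figure for an allocation effect on baseline scores. Assume the letter shifts the A minus B baseline difference by b = 0.02 to 0.05 z, and that a fraction k of the shift is still present at 24 months. Bias in the A minus B estimate is:

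- unadjusted change score: (k − 1) × b;
- analysis balanced on observed baseline, linear working model with follow-up-on-baseline slope s: (k − s) × b.

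| Scenario | Absolute bias, b = 0.02 | Absolute bias, b = 0.05 | Share of 0.105 |
|---|---|---|---|
| Change score, k = 0 | 0.020 | 0.050 | 19% to 48% |
| Change score, k = 0.5 | 0.010 | 0.025 | 10% to 24% |
| Change score, k = 1 | 0 | 0 | 0% |
| Balanced, s = 0.7 (assumed), k = 0 | 0.014 | 0.035 | 13% to 33% |
| Balanced, s = 0.7 (assumed), k = 1 | 0.006 | 0.015 | 6% to 14%, opposite sign |

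**Consequence in the first row only** (normal approximation, SE 0.0326). With no true effect, two-sided rejection rises from 5% to 9.4% (b = 0.02) or 33.6% (b = 0.05). With the planned effect and a shift that raises A's baseline, power falls from 89.7% to 74.2% or 39.3%. A shift that lowers A's baseline inflates the apparent effect to 0.125 or 0.155 z. A larger sample does not reduce the bias.

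**Can the analysis repair it?** Entropy balancing equalises what was recorded among those who reached baseline. If the recorded score is itself shifted by allocation, making the arms equal on it carries the share (k − s) × b into the estimate. Loss driven by unrecorded traits such as motivation is not balanced either. Multiple imputation has little to work with for patients who have no baseline battery.

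**The case against.** Several points on the other side have weight.

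- **Cluster design.** Once one patient in a practice is told the arm, site staff know it for every later patient there. A reader might infer that an envelope opened at the end of each baseline visit would keep interviewers blind. With 12 patients per practice it would not do so after the first disclosure. This stands and shapes the fix.
- **Unblinding at 24 months as well.** A shift that persists cancels in a change score (k = 1), and moving only the baseline would then leave the follow-up shift uncancelled. This is correct as arithmetic. Two distortions two years apart cannot be counted on to match, however, and unblinded follow-up is a separate weakness that this change does not claim to cure.
- **Structured testing.** Interviews are fully structured and interviewers are trained, which limits scoring latitude. It does not limit participant effort or withdrawal.
- **Openness.** The article admits that interviewers are unblinded. That may be unavoidable once the intervention is under way, but it does not explain telling participants before they are tested.

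Three other stronger readings go beyond the text. The rule that "scores will be calculated using baseline mean and standard deviations" is not a second bias route: with constants common to both arms, the mean cancels in the change and the SD only sets the unit. The entry "Personnel continuity regarding the contact person for the participants" in Table 1 is a motivational measure and does not say that this person gives the 24-month battery. Nor can one say that patients lost before baseline necessarily leave every analysis, since imputation is mentioned.

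**Conclusion.** The point holds as a flaw in sequence. The article sends the allocation letter before the baseline visit, so the only pre-treatment measurement of the primary endpoint is taken with the arm known to the participant and not concealed from the interviewer. Allocated patients can also be lost by arm before any score exists. The planned weighting and imputation cannot be relied on to repair this afterwards.

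Its size and direction cannot be derived from the documents. A reader might infer that the treatment estimate will be biased by 19% to 48% of the target. That range follows only from an assumed shift of 0.02 to 0.05 z, present at baseline and absent at 24 months, in an unadjusted change score. Under the other scenarios above it is smaller, and it is zero for a change score with full persistence. The loss before baseline is not quantified at all. The change is justified because the problem cannot be corrected after data collection and can be largely avoided by changing the order.

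**What to change.** 1. Disclose allocation only after the participant's baseline interview and test battery are completed and entered, and begin arm A delivery after that point.
2. Because the practice is the randomised unit, complete the baselines of all consented patients in a practice, where feasible, before releasing that practice's allocation to the site team. The list is already concealed from the sites, so this extends an existing arrangement. Where it is not feasible, state that the new order protects participant blinding and retention up to baseline, but not interviewer blinding after the first disclosure in a practice.
3. Report, by arm, the consented patients lost before baseline.

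The cost is mainly a changed mailing order and revised visit scripts. Arm A may start later or need a follow-on contact. Since its components are delivered face to face at home, for up to 576 participants, that may take staff time; the article gives no staffing figures from which to judge it. Waiting for a whole practice to finish baseline also delays its earliest participants.

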**Table 3 Tab3:**
[figure not shown]
Schedule of enrolment, interventions and assessments in the course of *AgeWell.de*

^1^: Telephone interim monitoring and booster sessions 2, 4, 8, 16, and 20 months after baseline-assessment in intervention group A; ^2^: Face-to-face intervention visit in intervention group A after 12 months; ^3^: limited assessment of the actual medication via telephone

### Data management

Each local recruiting center will enter collected data via an internet-based electronic data capture system which complies with the FDA requirements (21 CFR Part 11) as well as the guidelines for Good Clinical Practice (GCP). Data will be stored in a central Oracle-database. For statistical analyses, data can be exported via a web-based export-tool into SPSS, SAS, CDISC ODM, or similar.

The technical infrastructure includes the internet-based remote data entry system and the central database server. Data will not be stored locally. For transfers, data will be secured using 128 bit SSL encryption. Access to the database and webserver is controlled by two consecutive firewall systems. Data will only be stored using a pseudonym generated automatically upon first entry of a patient’s data into the database. Access to the electronic data entry system will be provided to members of the *AgeWell.de* study group according to a detailed concept of roles and rights.

### Statistical analyses

Preliminary analyses involve three parts. First, data will be cleaned and checked for inconsistencies by statisticians at the central data management center to ensure data accuracy and coherence. Second, outcome variables will be examined to identify potential outliers and leverage points. Third, missing data will be inspected and handled according to patterns of data missingness, e.g., by multiple imputation [65].

A dropout analysis will be performed to test whether complete and incomplete cases differ according to relevant sociodemographic variables, potentially introducing selection bias.

Descriptive analyses will be carried out to examine differences in baseline measurements regarding the composite cognitive *z-*score (primary endpoint) and secondary endpoints between the two intervention groups. Additionally, single scores for the six neurocognitive domains will be calculated and analyzed. Suitable balancing techniques, such as entropy balancing, will be used for baseline measurements to warrant a high degree of comparability between study groups [66]. In order to analyze changes in primary and secondary endpoints of the two groups over time (treatment effect), latent growth curve modeling (LGM) will be utilized. Group membership (A vs. B) as well as other time-invariant characteristics will be assessed as predictors of change in cognitive performance in the models. Model estimates will be weighted using, for example, calculated entropy balancing weights to equalize possible baseline differences in covariates and outcomes. The models will further be stratified by age and gender to evaluate whether treatment effects on primary and secondary outcomes differ by subgroups.

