### Sample size

Sample size calculations are based on a composite *z-*score of cognitive performance from previous findings in mild AD [61], i.e., a mean decrease in the composite *z-*score of cognitive performance of − 0.21 with a common SD of 0.5 is assumed in intervention group B during the two year follow-up period. Accordingly, the required sample size is estimated to be 475 participants per group in order to detect a 50% difference in change in the composite *z*-score between intervention groups (2-sided *t*-test for equal variances; with 5% significance level and 90% power). We assume an inflation factor of 1.1 (corresponding to an intra-cluster correlation coefficient of 0.02 and a cluster size of 6). In view of the findings from the FINGER trial, we further assume a dropout rate of no higher than 10% [5]. Therefore, a total sample size of *n* = 1,152 individuals (*n* = 576 per group) seems sufficient.

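### The stated primary model has no practice level or practice-clustered variance although practices are randomised; run as written at the protocol's ICC, its type I error is about 6.2 to 7.6%

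*Protocol article*

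**What the plan says.** Three parts of the protocol article bear on this.

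- **Randomization.** The practice is the unit: "Participating GP practices (clusters) will be randomized either to intervention A or B". Allocation is blocked, and no stratification by study site is mentioned.
- **Sample size.** Correlation within practices is expected. The sample is inflated by 1.1, "corresponding to an intra-cluster correlation coefficient of 0.02 and a cluster size of 6".
- **Statistical analyses.** For change in the primary and secondary endpoints, "latent growth curve modeling (LGM) will be utilized". On predictors: "Group membership (A vs. B) as well as other time-invariant characteristics will be assessed as predictors of change in cognitive performance in the models". On weighting: "Model estimates will be weighted using, for example, calculated entropy balancing weights to equalize possible baseline differences in covariates and outcomes". Models are also stratified by age and gender. Later in the section, cost-effectiveness is analysed with net benefit regressions.

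Nowhere does the analysis section mention a practice random effect, a multilevel structure, a cluster-robust variance or an analysis of practice means.

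**The concern.** The design allows for clustering, but the analysis as described does not. When whole practices are allocated, between-practice variation is part of the error of the treatment comparison. A model that treats patients as independent leaves it out. Standard errors are then too small, intervals too narrow, and the nominal 5% test rejects too often under the null.

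Nothing else in the described model makes up for this:

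- A growth model handles repeated scores within a person. It does not handle patients within a practice.
- Entropy-balancing weights align baseline covariates between arms. They do not put between-practice variation into the variance.
- The unnamed time-invariant predictors cannot include practice as a fixed effect, because each practice lies wholly in one arm and would be collinear with group.

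The same model form serves the primary and secondary endpoints, so all of those comparisons are affected. The uncertainty around the cost-effectiveness ratio is affected too if the net benefit regressions are run without allowance for practice.

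**Working it through.** **Inputs from the protocol.** ICC 0.02 and cluster size 6 (Sample size); 96 practices and 12 patients per practice (Recruitment procedure); 1,152 patients, 10% dropout, two-sided 5% level, 90% power, control change −0.21, SD 0.5, and a 50% difference to be detected (Sample size). I take the ICC to apply to the change score, since that is what the sample size is built on.

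**Reproducing the plan's sample size.**
- Difference to detect: 0.5 × 0.21 = 0.105.
- n per arm = 2 × (1.960 + 1.282)² × 0.5² / 0.105² ≈ 477 (478 with the exact t-test). The protocol gives 475.
- Design effect: DE = 1 + (m − 1) × ICC = 1 + 5 × 0.02 = 1.10, as stated.
- 475 × 1.1 = 522.5. Dividing by 0.9 gives 581; multiplying by 1.1 gives 575. The protocol gives 576.

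The sample size therefore reproduces closely, with clustering counted at DE 1.10.

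**Cluster sizes.** The sample size uses m = 6. Recruitment implies 1,152 / 96 = 12. After 10% dropout, 1,152 × 0.9 / 96 = 10.8 are analysed.

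**Effect of ignoring practice.** The naive standard error is the correct one divided by √DE. It is therefore too small by 1 − 1/√DE, and the actual two-sided error is 2 × [1 − Φ(1.96/√DE)].

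| Patients per practice | DE at ICC 0.02 | SE too small by | Type I error |
|---|---|---|---|
| 6 | 1.100 | 4.7% | 6.2% |
| 10.8 | 1.196 | 8.6% | 7.3% |
| 12 | 1.220 | 9.5% | 7.6% |

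For example, at m = 12: 1.96 / √1.22 = 1.775, and 2 × [1 − Φ(1.775)] = 0.076.

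**Range over assumed ICCs.** The protocol gives only 0.02. At ICC 0 the error is 5.0% for any m. At 0.005 it is 5.3% (m = 6) to 5.6% (m = 12). At 0.05 it is 8.0% (m = 6) to 11.5% (m = 12).

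**Simulation under the null** (20,000 runs per setting, ICC 0.02). A t-test ignoring practice rejected in 7.9% of runs with 96 practices of 12, and in 6.2% with 192 practices of 6. A t-test on practice means rejected in 5.2% and 5.0%.

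**Which practice term is needed.** The endpoint is change, and only baseline and 24 months are assessed in both arms. Write the score as practice level + person level + time effects + residual. A practice intercept on level is the same at both visits and cancels from each person's change. With complete data, the group-by-time test then reduces to the t-test on individual changes, which is the naive test above. Between-practice variation in change enters only through a practice-level effect on the slope, or through a practice intercept when change itself is the outcome.

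**The case against.** The strongest reply is that this is silence and not a stated error. The document is a journal article, and a fuller protocol or an analysis plan may exist. Its analysis section is written as an outline, with imputation and balancing methods given only as examples and covariates unnamed. The sentence on group membership lists predictors, whereas a practice random effect or a clustered variance belongs to the error structure, so the list does not rule either out. The authors plainly know the trial is clustered.

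Much of this stands. A reader might infer that the model is single-level by design, or that the trial's reported type I error will exceed 5%. The article supports neither: it does not say that patients will be treated as independent, and the excess requires both that practice is ignored and that the true ICC is above 0. A reader might also treat the absence of a study-site term or of small-sample degrees of freedom as an error. It is not: no stratification by site is described, and with 96 practices the critical value (t on 94 df, about 1.99) is close to 1.96. The mismatch between 6 and 12 patients per practice is a separate matter, so both figures are shown here.

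The reply does not remove the point. The section goes as far as naming the model, the predictors, the weighting and the strata for the treatment effect. Whether that test respects the unit of randomisation decides whether it is valid, and is more than a detail of execution. An analyst following the text would run an anti-conservative test under the protocol's own ICC.

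**Conclusion.** The point holds for the model as stated. Practices are randomised and the protocol itself expects an ICC of 0.02, yet neither the latent growth model nor the net benefit regressions are given a practice level or a practice-clustered variance. Run as written, the primary test has a type I error of about 6.2% at the cluster size in the sample size section, and 7.3 to 7.6% at the cluster sizes implied by recruitment. The excess is moderate. The figures assume that the ICC applies to change, that practices are of equal size, and that the weights add no further variance. Because the primary test is affected and the error runs towards false positives, it should be settled before analysis. If an existing analysis plan already deals with practice, it is enough for the protocol to say so.

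**What to change.** State that all between-arm analyses, including the net benefit regressions, account for GP practice in one of two ways:

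- practice-clustered (cluster-robust) standard errors; or
- a multilevel growth model with a practice-level random effect on the slope. A practice random intercept alone is enough only if the change score itself is the outcome.

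Report the observed ICC for the primary endpoint. A study-site term is optional.

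The cost is a short paragraph of wording and no new data. Intervals become slightly wider: at ICC 0.02, by a factor of √1.10 = 1.05 with 6 per practice, up to √1.22 = 1.10 with 12. With 576 × 0.9 = 518 analysed per arm, power for the planned 0.105 is about 90% at DE 1.10 and about 87% at DE 1.196.
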